### Sample Size Estimation

Our primary outcome measure for this trial is progression from early AKI (RIFLE class - **RISK**) to a more severe form of AKI, defined by progression in AKI to the development of either RIFLE class - **Injury or Failure**. Based on data from a large observational study, an estimated 60% of critically ill patients with early AKI worsen and develop further kidney injury[46]. We estimate that furosemide will contribute to a 20% absolute reduction in the proportion of those patients who progress from early AKI (RIFLE class - **RISK**) to either RIFLE class - **Injury or Failure**. This would require a total sample size of 214 patients and provide 80% power (alpha 0.05) for detection of a 20% difference in the proportion with progression of AKI. An estimated 50% of patients developing early AKI will have sepsis[47]. Randomization will be stratified by the presence of sepsis. The total sample size was increased to 216 patients to ensure a balanced number of patients in each treatment arm (Figure 1).

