### Statistical Analysis

The primary analysis will evaluate the proportion of critically ill patients with early AKI that have progression in kidney injury by having received furosemide or placebo. Analysis will be intention-to-treat.

The secondary analysis will evaluate for differences between furosemide and placebo in cumulative fluid balance and in the largest changes to serum potassium, serum magnesium, serum pH and serum bicarbonate levels, defined as difference from enrollment to lowest documented level during study infusion. In addition, this secondary analysis will evaluate for differences in the need for RRT, duration of AKI, rate of renal recovery and hospital mortality.

Descriptive statistics, boxplots and histograms will be used to analyze individual baseline variables by having received furosemide or placebo. Normally or near normally distributed, non-correlated variables will be reported as means with standard deviations (SD) and compared using the appropriate Student's t test. Non-normally distributed, non-correlated continuous data will be reported as medians with inter-quartile ranges (IQR) and compared using the Mann Whitney U test. Non-correlated categorical data, including the primary outcome, and need for RRT, renal recovery and hospital mortality, will be reported as proportions and compared using Fisher's Exact Test. If necessary, multi-variable logistic or linear regression will be used to control for potential confounding from imbalances in baseline characteristics after randomization.

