The tertiary analysis will evaluate for differences between furosemide and placebo in the change of novel serum and urine biomarkers for AKI, defined by absolute levels and relative to baseline (enrollment) at 12 hours, 24 hours and at the time of initiation of RRT, renal recovery or ICU discharge. All samples will remain blinded during processing, storage and analysis. Normally distributed correlated data will be analyzed by the repeated measures ANOVA. Non-normally distributed correlated data will be analyzed by the Friedman test. Correlated categorical data will analyzed by generalized estimating equations. The diagnostic and predictive characteristics of absolute values and relative changes in novel serum and urine biomarkers for progression of AKI as well as need for RRT will be evaluated by 2 x 2 tables and construction of receiver operator characteristic curves. A p-value of < 0.05 will be considered significant. All statistical tests will be two-sided.

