### Potential Challenges with the Trial

Research in patients with AKI has been traditionally challenging due to lack of a standardized definition or classification scheme for AKI. In order to address this issue, and optimize the potential generalizability, we have incorporated the RIFLE definition/classification system for AKI[42]. This consensus definition has now been validated and its clinical use is strengthened by its objectivity, simplicity and by the incorporation of a system to categorize the changes in severity of AKI over time.

The development of acute pulmonary edema in an ICU patient with AKI was identified in our survey as an indication for urgent furosemide or RRT and as such a potential barrier to compliance with our trial[20]. We have addressed this in our protocol by including a provision for the urgent use of furosemide in any enrolled patient with pulmonary edema at the discretion of the consultant ICU physician. Similarly, RRT can be initiated at any time.

Another potential issue with the protocol was the handling of an excess diuresis following initiation of the study drug. To address this, we have incorporated into our study algorithm provisions to temporarily discontinue the study drug in the event of an excess diuresis. Similarly, electrolyte abnormalities, in particular low magnesium and potassium, are common with use of furosemide. This issue is addressed by our ICU having standardized protocols for the replacement of both of these electrolytes in the event they are significantly low.

We do not anticipate any losses to follow-up during the study intervention. This is due to our primary outcome, progression in severity of kidney injury in AKI, being measured while the patient is admitted to ICU. A situation may arise where a patient is randomized and allocated as non-septic but subsequently develops sepsis during the trial. We will address this potential issue by analyzing all these patients according to their initial allocated group.

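### Randomisation is stratified by sepsis, but the named primary test ignores the stratum and adjustment waits on observed imbalance: valid and adequately powered, but improvable at no cost

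*Protocol article*

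**What the plan says.** All references are to the protocol article.

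- **Randomisation.** Sample Size Estimation states: "Randomization will be stratified by the presence of sepsis". Study Design, Setting and Patient Population and Methods of Randomization, Concealment and Blinding say the same.
- **Primary test.** Under Statistical Analysis, non-correlated categorical data, with the primary outcome listed by name, "will be reported as proportions and compared using Fisher's Exact Test". Sepsis is not mentioned there.
- **Adjustment.** The same section continues: "If necessary, multi-variable logistic or linear regression will be used to control for potential confounding from imbalances in baseline characteristics after randomization".
- **Late sepsis.** Potential Challenges with the Trial takes up patients randomised as non-septic who later become septic, and proposes "analyzing all these patients according to their initial allocated group".
- **Design figures.** Sample Size Estimation takes it that "an estimated 60% of critically ill patients with early AKI worsen and develop further kidney injury" and expects furosemide to bring a "20% absolute reduction in the proportion of those patients who progress from early AKI". It asks for 214 patients for 80% power at alpha 0.05, raised to 216 for balance. Statistical Analysis adds: "All statistical tests will be two-sided".

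**The concern.** A factor used to stratify randomisation would normally be carried into the primary analysis. Stratifying equalises the arms on sepsis. If sepsis affects progression, the true variance of the difference between arms is then smaller than an unstratified test assumes, and the test becomes conservative. Fisher's exact test is conservative in any case. Together they could leave some of the information in 216 patients unused.

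The second issue is the trigger for adjustment. After a sound randomisation, baseline imbalance is chance. The better reason to adjust for a covariate is that it predicts outcome, which can be decided in advance. A model that runs only if the observed baseline table looks uneven has a form that depends on the data.

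Both are choices that the article states, so neither is merely a detail deferred to a fuller document.

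**Working it through.** **Inputs from the article.** Control risk 60%; treated risk 60% − 20% = 40%; two-sided alpha 0.05; power 80%; 216 patients, read as 108 per arm; about 50% septic, so 54 per arm in each stratum.

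**Input not in the article.** The difference in progression risk between septic and non-septic patients, called d. It is assumed at 0 to 40 percentage points, with control risks 60% ± d/2.

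**Step 1: reproduce 214.** Without continuity correction, with mean risk 0.5:

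n = [1.96·√(2·0.5·0.5) + 0.8416·√(0.6·0.4 + 0.4·0.6)]² / 0.20² = (1.3859 + 0.5831)² / 0.04 = 96.9, so 97 per arm, 194 in total.

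With continuity correction:

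n′ = (n/4)·[1 + √(1 + 4/(n·0.20))]² = (96.9/4)·(1 + 1.0983)² ≈ 106.7, so 107 per arm, 214 in total.

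The corrected formula matches the article exactly. It approximates Fisher's test, so sample size and named test agree. The allowance for Fisher is 214 − 194 = 20 patients.

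**Step 2: exact properties of Fisher's test.** Full binomial enumeration gives power of 79.5% at 107 per arm and 80.2% at 108. True size at 108 per arm is 3.5% at a common risk of 50% and 3.6% at 60%. Uncorrected chi-square at 108 per arm has 83.8% power and size of 4.8% to 4.9%.

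**Step 3: stratified test.** With x control-arm events and m total events in a stratum, the Mantel-Haenszel test without continuity correction uses D = Σ(x − m/2) and V = Σ 54²·m·(108 − m)/(108²·107), rejecting when |D|/√V > 1.96. Each row below is from 400,000 simulated trials, with a common odds ratio and marginal risks of 60% and 40%. A common risk difference gives the same power to within about 0.1 point.

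| d (points) | Fisher power | Chi-square power | Stratified power | Fisher to chi-square | Chi-square to stratified | Fisher size | Stratified size |
|---|---|---|---|---|---|---|---|
| 0 | 80.2% | 83.8% | 83.8% | 3.6 | 0.0 | 3.6% | 4.8% |
| 10 | 80.3% | 84.0% | 84.0% | 3.7 | 0.1 | 3.5% | 4.9% |
| 20 | 80.7% | 84.3% | 85.2% | 3.6 | 0.9 | 3.2% | 5.1% |
| 30 | 81.4% | 85.0% | 87.7% | 3.6 | 2.7 | 2.7% | 5.0% |
| 40 | 82.4% | 86.0% | 90.1% | 3.6 | 4.1 | 2.1% | 5.0% |

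The two gain columns are in percentage points and were taken before the powers were rounded.

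**Step 4: hand check at d = 40, common risk difference.** Control risks are 0.4 and 0.8, treated risks 0.2 and 0.6, and pooled stratum risks 0.3 and 0.7. The mean within-stratum variance is 0.21 under the null and 0.20 in each arm under the alternative. Standard errors are √(2·0.21/108) = 0.0624 and √(2·0.20/108) = 0.0609. Then z = (0.20 − 1.96·0.0624)/0.0609 ≈ 1.28, a power of about 90%, in line with the simulation.

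**Step 5: continuity correction.** If the stratified test is run with a 0.5 correction, its power falls to 80.2%, 80.4%, 81.7%, 84.5% and 87.2% across the five rows, with size about 3.4% to 3.6%. The gain from leaving Fisher is then lost, so the wording has to exclude the correction.

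**The case against.** The strongest defence is that nothing here is broken. The sponsor asked for 80% power, sized the trial for a conservative test, named that test, and gets 80.2%. A conservative exact test that the sample size already allows for is a defensible choice. This stands, and it rules out several stronger readings.

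- **The trial is underpowered, or loses power it was sized to have.** Step 1 shows that the 20-patient allowance for Fisher's conservatism is already in the 214.
- **Ignoring the stratum invalidates the test.** The error is towards conservatism, and type I error is not inflated.
- **The nominal 5% test really runs near 2%.** That needs a 40-point sepsis effect. The article gives a sepsis prevalence but no progression risk by sepsis. Its own figures support about 3.5%.
- **The loss comes mainly from ignoring sepsis.** Up to d = 20 nearly all of the gain comes from leaving Fisher, as a plain chi-square test would show. Only at 40 points does the stratum contribute as much.
- **The conditional regression creates a second primary answer.** One test is named for the primary outcome. The regression sentence covers linear as well as logistic models, so it reaches other outcomes too, and it does not say that regression replaces Fisher. It reads as a supplement.

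An article may also leave a covariate list or an imbalance threshold to a fuller document, so their absence is not held against it. The sentence on late sepsis suggests that some analysis by randomised stratum may be intended elsewhere. Neither point changes what is stated here: the named primary test uses no stratum, and observed imbalance is the stated reason to adjust.

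**Conclusion.** The point holds as a recommended improvement, not as the correction of an error. At 216 patients, a sepsis-stratified Mantel-Haenszel test without continuity correction would raise power from 80.2% to about 84% if sepsis is not prognostic, and to between 84% and 90% for assumed sepsis effects of 10 to 40 points, while keeping size near 5%. About 3.6 points of that come from dropping Fisher's conservatism. The stratum adds under 1 point up to a 20-point effect, then 2.7 and 4.1 points at 30 and 40. In none of the scenarios examined does the stratified test have lower power than Fisher.

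These figures assume 1:1 allocation, equal strata, no missing outcomes and the article's 60% versus 40%. The sepsis effect is an assumption throughout.

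The objection to imbalance-triggered adjustment needs no assumed figure, but it concerns a supportive analysis.

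**What to change.** 1. Make the primary analysis a Mantel-Haenszel comparison stratified by sepsis as randomised, without continuity correction, reported with the risk difference and its 95% CI.
2. Keep the unstratified Fisher's exact test as a sensitivity analysis.
3. Replace the conditional regression for the primary outcome with one supportive logistic model. It should contain the sepsis stratum and any further baseline covariates chosen beforehand for prognostic value, be run whatever the observed imbalance, and be labelled secondary to the primary test.
4. State that patients who become septic after randomisation stay in their randomised stratum in these analyses, which fits the existing sentence on late sepsis.

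The cost is a change of analysis wording before unblinding. The stratum is known for every patient at randomisation, baseline data are already collected at enrolment, and the sample size need not change.

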### Operational Definitions

#### Acute kidney injury (AKI)

The operational definition for early AKI will be defined and classified according to a modified RIFLE criteria (acronym indicating Risk of renal dysfunction; Injury to the kidney; Failure of kidney function; Loss of kidney function; and End-stage kidney disease) as outlined by the ADQI Working Group [42]. In brief, the RIFLE criteria classifies AKI into three categories of severity (Risk, Injury, and Failure) and two categories of clinical outcome (Loss and End-stage kidney disease) based on relative changes to serum creatinine and urine output. The presence of early AKI will be defined by a minimum of *RIFLE class - RISK*: an abrupt (within 7 day) reduction in kidney function characterized by an relative increase in serum creatinine of ≥ 50% (1.5 fold) or an absolute increase of ≥ 26.5 μmol/L from baseline or a reduction in urine output of ≤ 0.5 mL/kg/hr for ≥ 6 hours. For reference, the RIFLE category INJURY is defined as a relative increase in serum creatinine ≥ 100% (2.0 fold) or a reduction in urine output of ≤ 0.5 mL/kg/hr for ≥ 12 hours. The RIFLE category FAILURE is defined as a relative increase in serum creatinine ≥ 200% (3.0 fold) or an absolute value ≥354 μmol/L (accompanied by an acute increase ≥44.2 μmol/L) or a reduction in urine output of ≤0.3 mL/kg/hr for ≥ 24 hours or anuria for ≥ 12 hours.

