**Figure 2 F2:**
[figure not shown]
**Overview of the SPARK study drug infusion algorithm**.

The study infusion bag will contain 2000 mg of furosemide in 500 mL of 0.9%NaCl for a final concentration of 4 mg/mL. The appearance of the study infusion bags for furosemide and placebo will be identical and there will be no marking on the infusion bags other than a 4-digit coded identifying study number. This will minimize bias and ensure blinding of allocation by the study investigators, research coordinator, ICU physicians and all involved health care providers.

The continuous infusion will be titrated to achieve a target urine output in the range of 1.0-2.0 mL/kg/hr. The treatment algorithm for titration of the continuous infusion is shown in Figure 2. Each patient will be administered a loading dose of 0.4 mg/kg as a separate infusion bag followed by a continuous infusion commenced at a dose of 0.05 mg/kg/hr (Table 1). The maximum infusion rate will be 0.40 mg/kg/hr. The urine output will be assessed hourly. If the target urine output has been achieved, then the current infusion rate will be continued. If the target urine output has not been achieved, the dose will be increased to the next infusion rate in the algorithm. If the urine output is too brisk (>2 mL/kg/hr x 2 hrs), the infusion rate will be reduced. If the urine output is still >2 mL/kg/hr AND the infusion rate is at the lowest rate, the study drug will be discontinued infusion until the urine output is <1 mL/kg/hr. If any of the following criteria are fulfilled: decrease in mean arterial pressure <65 AND/OR addition of or an increase in vasoactive requirements of ≥20% to achieve goal mean arterial pressure OR central venous pressure <8 cmH2O OR central venous oxygen saturation <60% OR a cardiac index <2.0 L/min/1.73 m^2 ^(if measured) at any time, the consultant ICU physician and ICU team will be notified to review the patient.

**Table 1 T1:** Summary of weight-based categories for commencement for study infusion rate (concentration study drug 4 mg/mL)

Weight Category (kg)	Bolus loading dose	Start infusion dose	Start infusion dose (mg/hr)	Start infusion rate (mL/hr)
≤50	0.4 mg/kg	0.05 mg/kg/hr	2.5	0.6

55	0.4 mg/kg	0.05 mg/kg/hr	2.8	0.7

60	0.4 mg/kg	0.05 mg/kg/hr	3.0	0.8

65	0.4 mg/kg	0.05 mg/kg/hr	3.3	0.8

70	0.4 mg/kg	0.05 mg/kg/hr	3.5	0.9

75	0.4 mg/kg	0.05 mg/kg/hr	3.8	0.9

80	0.4 mg/kg	0.05 mg/kg/hr	4.0	1.0

85	0.4 mg/kg	0.05 mg/kg/hr	4.3	1.1

90	0.4 mg/kg	0.05 mg/kg/hr	4.5	1.1

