### Data Collection

Detailed clinical, procedure-related, physiologic and laboratory data will be collected. Blood and urine will be collected at baseline, 12 hours, 24 hours and daily thereafter until participants exits the study. Data will be collected on standardized CRFs developed by the EPICORE centre. Completed CRF will be returned to the EPICORE centre, entered into a central database, where data queries will be generated.

Clinical data captured will include demographics, co-morbidities and prescribed/current drug therapy. Details of admission diagnoses, surgical status, and dates of hospital and ICU admission will be recorded. Detailed data will be recorded on date of enrollment (i.e. fulfilling criteria for early AKI). This will include details of interventions (i.e. mechanical ventilation, vasoactive drugs, fluid therapy), hemodynamics (i.e. blood pressure, heart rate, central venous pressure), and acute physiology (i.e. components of severity of illness scores, urine output, fluid balance, secondary non-kidney organ dysfunction). During the trial, data will be collected daily on urine output, fluid balance, electrolytes, acid-base status, serum creatinine and urea. Collected blood and urine samples will be stored for batched analysis of kidney-injury specific biomarkers, including: serum and urine cystatin C, serum and urine neutrophil gelatinase-associated lipocalin (NGAL), urine interleukin-18 (IL-18); urine kidney injury molecule-1 (KIM-1), and urine L-type fatty acid binding protein (L-FABP).

Data will be collected each day on whether the primary endpoint (progression of AKI) has occurred, for evidence of any secondary endpoints and for criteria for trial discontinuation.

Finally, any study protocol violations will be recorded. The adjudication of protocol violations will be determined by a study investigator blinded to the treatment allocation.

All enrolled patients will be followed to determine the duration of AKI, continued need for RRT, renal recovery and mortality until death or discharge from hospital and at 30, 60 and 90-days after randomization.

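### Urine biomarkers are compared between arms with no correction for urine flow, so dilution alone can lower them on furosemide wherever the arms separate in flow

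*Protocol article*

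**What the plan says.** All references are to the protocol article.

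- **Comparison (Statistical Analysis).** "The tertiary analysis will evaluate for differences between furosemide and placebo in the change of novel serum and urine biomarkers for AKI". The measure is "defined by absolute levels and relative to baseline (enrollment) at 12 hours, 24 hours", and also at the start of RRT, renal recovery or ICU discharge.
- **Second use of the same measures (Statistical Analysis).** "The diagnostic and predictive characteristics of absolute values and relative changes in novel serum and urine biomarkers for progression of AKI", and for need for RRT, are to be examined with 2 x 2 tables and ROC curves.
- **Markers (Data Collection).** Cystatin C and NGAL are measured in serum and urine. The markers measured in urine only are "urine interleukin-18 (IL-18); urine kidney injury molecule-1 (KIM-1), and urine L-type fatty acid binding protein (L-FABP").
- **Sampling (Data Collection).** "Blood and urine will be collected at baseline, 12 hours, 24 hours and daily thereafter until participants exits the study". No timed urine collection is described.
- **Intervention (Study Intervention).** "The continuous infusion will be titrated to achieve a target urine output in the range of 1.0-2.0 mL/kg/hr". Urine output is checked every hour for this purpose, while Data Collection lists urine output among the data gathered daily.
- **Entry (Operational Definitions, Acute kidney injury).** One of three alternative routes to RISK is "a reduction in urine output of ≤ 0.5 mL/kg/hr for ≥ 6 hours". The other two rest on creatinine.

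Neither Data Collection nor Statistical Analysis relates a urine marker to urine creatinine, urine volume or excretion rate.

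**The concern.** The concentration of a marker in urine depends on how much the kidney excretes and on how much water it is excreted in. The study drug acts on the second quantity by design. The Background also cites a systematic review in which loop diuretics gave a greater rise in urine output (OR 2.6, p = 0.004). The trial therefore expects its arms to differ in the quantity that sets concentration.

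The resulting bias runs in the direction of the hypothesis. The Background proposes that furosemide may lessen early kidney injury, and dilution would look the same: lower injury markers on furosemide. Blinded handling of samples does not guard against it. The Discussion says the results should help to design a phase III trial, so a spurious biomarker signal could carry weight there.

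The ROC analysis has a related difficulty. Progression to Injury or Failure can be met on low urine output. In samples taken after the infusion starts, low flow both concentrates the marker and helps to meet the outcome, so part of the apparent prediction may be flow.

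**Working it through.** **The plan's own figure.** The article gives no figure for the biomarker analysis. Its only related number is the sample size, which supplies the arm size used below. For 60% v 40%, two-sided alpha 0.05 and 80% power:

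- Uncorrected n per arm = [1.96 × √(2 × 0.5 × 0.5) + 0.842 × √(0.6 × 0.4 + 0.4 × 0.6)]² / 0.20² = 96.9, so 97 per arm.
- With continuity correction: (96.9/4) × [1 + √(1 + 4/(96.9 × 0.20))]² = 106.7, so 107 per arm and 214 in total.

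This matches the stated 214, which was raised to 216. I take 108 per arm, assuming equal allocation.

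**Step 1: the identity.** Let E be the excretion rate, V the urine flow and C = E/V the concentration. If E is equal in the two arms (no effect on injury), then

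C(furosemide) / C(placebo) = V(placebo) / V(furosemide).

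**Step 2: does change from enrolment help?** The relative change in one arm is C(t)/C(0) = [E(t)/V(t)] × [V(0)/E(0)]. Randomisation makes E(0) and V(0) alike on average, so they cancel between arms. What remains is again V(placebo, t) / V(furosemide, t). The same holds for an arithmetic difference: the enrolment value cancels and the post-baseline dilution stays.

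**Step 3: size.** Furosemide flow is set across the target range. Placebo flow after randomisation is not given in the article and is assumed. Concentration ratio, furosemide/placebo:

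| Placebo flow (mL/kg/hr, assumed) | Furosemide 1.0 | Furosemide 1.5 | Furosemide 2.0 |
|---|---|---|---|
| 0.5 | 0.50 | 0.33 | 0.25 |
| 0.75 | 0.75 | 0.50 | 0.38 |
| 1.0 | 1.00 | 0.67 | 0.50 |

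**Step 4: would such a ratio be called significant?** This uses a normal approximation on the log scale with 108 per arm, SE = SD × √(2/108), and assumed log-SDs of 1.0 to 2.0. Example, ratio 0.50 and log-SD 1.5: SE = 1.5 × 0.1361 = 0.204; |ln 0.50| / SE = 0.693/0.204 = 3.40; 3.40 − 1.96 = 1.44; probability 0.92.

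| True ratio from dilution alone | log-SD 1.0 | log-SD 1.5 | log-SD 2.0 |
|---|---|---|---|
| 0.50 | >0.99 | 0.92 | 0.72 |
| 0.75 | 0.56 | 0.29 | 0.18 |
| 1.00 (no flow difference) | 0.05 | 0.05 | 0.05 |

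**Step 5: after correction.** Excretion rate is C × V = E, so flow cancels. The ratio to urine creatinine in the same sample divides two quantities diluted equally, so flow cancels there too. Under pure dilution the ratio between arms is then 1.00 and the error rate returns to the nominal 5%.

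**The case against.** **The article never uses the word concentration.** One phrase covers serum and urine markers and contrasts the value at a time point with the change from enrolment. A creatinine-indexed marker would also have a level and a change, and assay detail is often left to a fuller document. This stands in part: concentration is an inference, though the natural one. The article does name the measures to be compared, and read as written both are open to dilution. The point is therefore about a definition that is stated, not about missing detail.

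**The arms may not separate much in flow.** Placebo runs under the same algorithm to the same target. Patients may enter on creatinine alone and must have met resuscitation goals. Open-label furosemide is permitted when judged urgent, the infusion is reduced or stopped when output is too high, and some furosemide patients may not reach target. This stands. A reader might infer that dilution is bound to produce a fall. The documents do not support that: the table in Step 3 includes a ratio of 1.00.

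**A fall of 50-75% is not a general between-arm figure.** A reader might take it from moving flow from 0.5 to 1.0-2.0 mL/kg/hr. That is a change within an oliguric patient. It becomes the between-arm difference only if placebo patients stay at 0.5. At a placebo flow of 0.75 the fall is 25-62%, and at 1.0 it is 0-50%.

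**The ROC effect is unquantified.** This stands. The article does not say which time points feed the curves, and enrolment samples carry no study-drug dilution.

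**The correction may need more than wording.** This also stands. Output is assessed hourly at the bedside, but the data list says daily, so hourly volumes may not reach the case-report form.

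**Conclusion.** The point holds as a conditional bias. As written, the between-arm comparison of five urine markers is open to dilution caused by the treatment, in the direction that favours furosemide, and change from enrolment does not cure it. At equal excretion the concentration ratio runs from about 0.25 to 1.00 over assumed placebo flows of 0.5-1.0 mL/kg/hr with furosemide on target. The actual size depends on how far the arms separate in flow, which the article cannot tell us. The significance probabilities rest further on assumed log-SDs and on all 216 patients contributing, so they only illustrate that even a modest ratio of 0.75 exceeds the nominal 5%. Post-baseline ROC curves may be affected; curves from enrolment samples are not affected by study-drug dilution.

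The reach is limited. This is a tertiary endpoint, and the point leaves serum cystatin C and serum NGAL, the primary and secondary analyses and the sample size untouched. It is worth settling before unblinding, because the bias has a direction and the remedy is cheap.

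**What to change.** In Statistical Analysis, base the between-arm urine biomarker comparison, and any ROC curve or 2 x 2 table using post-baseline urine, on two flow-corrected measures reported alongside raw concentration:

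1. Excretion rate: concentration times urine output over the interval around the sample. Use the hourly bedside volumes if the case-report form retains them, otherwise the daily volume.
2. The ratio to urine creatinine measured in the same stored sample.

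State that a fall in concentration alone will not be read as reduced injury. In Data Collection, say which urine volumes are kept with each sample. State which time points feed the ROC curves.

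**Cost.** Some extra data capture for the volumes, or one routine assay on urine already stored. Neither measure is perfect. Creatinine indexing is unreliable while kidney function is changing, and a daily volume is a coarse match for a 12-hour sample. That is the reason to show both. Serum biomarkers stay as planned, and no change to sample size, visits or treatment is needed.

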## Objectives

The specific objectives of this trial are:

• To compare the efficacy and safety of a continuous infusion of furosemide versus placebo titrated to the physiology parameter of urine output in early AKI on the primary outcome of progression in severity of kidney injury from early AKI.

• To evaluate the impact of furosemide versus placebo on key secondary endpoints including: fluid balance; electrolyte and acid-base balance; the need for RRT; total duration of AKI; the rate of renal recovery; and mortality.

• To evaluate the impact of furosemide versus placebo on the tertiary endpoint of differences, trajectory and prognostic value of novel serum and urine biomarkers for AKI.

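### The Friedman test named for non-normal repeated biomarker data has no treatment-arm term, so it does not test the furosemide-placebo contrast that the tertiary analysis sets

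*Protocol article*

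**What the plan says.** All references are to the protocol article. The third bullet under Objectives is comparative: "To evaluate the impact of furosemide versus placebo on the tertiary endpoint of differences, trajectory and prognostic value of novel serum and urine biomarkers". The Statistical Analysis section repeats the contrast: "The tertiary analysis will evaluate for differences between furosemide and placebo in the change of novel serum and urine biomarkers for AKI". The values, absolute and relative to enrollment, are to be examined "at 12 hours, 24 hours and at the time of initiation of RRT, renal recovery or ICU discharge".

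The same paragraph then assigns methods by data type. For normal repeated data: "Normally distributed correlated data will be analyzed by the repeated measures ANOVA". For the rest: "Non-normally distributed correlated data will be analyzed by the Friedman test". The Mann-Whitney U test appears earlier in that section, but only for non-normal data that are not correlated.

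Under Data Collection the sampling times are fixed: "Blood and urine will be collected at baseline, 12 hours, 24 hours and daily thereafter until participants exits the study".

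**The concern.** The trial has two parallel arms, and each patient receives one infusion throughout. Arm is therefore a between-patient factor. The Friedman test is a one-sample, within-patient procedure that compares repeated conditions in a single set of subjects. An analyst who followed the sentence literally for a non-normal marker would obtain a p-value for change over time, not for furosemide against placebo.

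Two misreadings could follow. A significant pooled result could be reported as a treatment effect when both arms simply changed together. Or the test could be run in each arm and a significant result in one set against a non-significant result in the other, as if that showed a difference.

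A second difficulty concerns the last time point. Starting RRT, recovering kidney function and leaving the ICU happen after randomisation, at different clock times in different patients and possibly in different proportions by arm. A patient who dies before any of them has no such value. The Friedman test needs a complete set of values for each patient at times that mean the same thing for all.

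**Working it through.** **Inputs.** From the protocol: two parallel arms; 216 patients, taken as 108 per arm; two-sided significance level 0.05; biomarker times at baseline, 12 h, 24 h and an event. The protocol gives no figure for the biomarker analysis, so there is none to reproduce. Its sample size concerns the primary outcome and has no bearing here.

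**Step 1: structure of the statistic.** For n patients and k times, rank the k values within each patient and let R_j be the sum of ranks at time j. Without ties,

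Q = [12 / (n k (k+1))] × Σ R_j² − 3n(k+1).

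No arm index appears. This was checked on 216 simulated patients at three times. Q = 1.843 on 2 degrees of freedom, so p = exp(−1.843/2) = 0.398. Q is identical after the patients are shuffled across arm labels. It is also identical after every value in one arm is multiplied by 5. This step needs no assumption about variances.

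**Step 2: pooled use.** The simulation assumed a log-normal marker, between-patient log SD 1.0, within-patient log SD 0.7, times baseline/12 h/24 h, a linear change on the log scale, 108 per arm and 2,000 runs. The comparator is Mann-Whitney U on log change from baseline to 24 h.

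| Assumed change to 24 h (log units) | Pooled Friedman rejects | Mann-Whitney rejects |
|---|---|---|
| +0.25 in both arms (no arm difference) | 80.9% | 6.0% |
| +0.35 in one arm, −0.35 in the other | 3.9% | 99.95% |
| none in either arm | 5.6% | 4.9% |

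The second row is the extreme case, chosen so that the two trends cancel. The percentages depend on the assumed SDs and changes. The structural result in Step 1 does not.

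**Step 3: per-arm use.** If the arms do not differ and each arm's test rejects with probability p, exactly one arm is significant with probability p(1−p) + (1−p)p = 2p(1−p).

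- p = 0.05: 2 × 0.05 × 0.95 = 9.5%
- p = 0.50: 2 × 0.50 × 0.50 = 50% (the maximum)
- p = 0.80: 2 × 0.80 × 0.20 = 32%
- p = 0.95: 2 × 0.95 × 0.05 = 9.5%

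In the first simulated scenario the per-arm rejection rates were 50.2% and 51.0%. The formula then gives 0.502 × 0.490 + 0.510 × 0.498 = 0.246 + 0.254 = 0.500, and the observed discordance was 50.2%. This confirms the formula. It does not show that p is near 0.50 in this trial.

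**Step 4: the normal-data branch.** Repeated measures ANOVA can include an arm factor and an arm-by-time term. The defect therefore lies in the non-normal branch only.

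**The case against.** The strongest reply is that the section already holds a valid test. At a single time, such as 24 h, each patient contributes one change score, and those scores are independent between patients. The rule assigning non-normal, non-correlated data to Mann-Whitney U could be read to cover them, and in the simulation above that test behaves well. A Friedman test within an arm can also describe change over time, which is relevant because the objective mentions trajectory.

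Part of this stands. A reader might infer that the trial could get no valid between-arm biomarker answer; that is too strong, because single-time change scores could be compared properly. But the reply does not rescue the text. The paragraph that sets the between-arm biomarker question deals with repeated measurements and sends the non-normal ones to Friedman, while Mann-Whitney is reserved for uncorrelated data. Nor is this a detail left to an analysis plan: a method is named, and a later plan would have to depart from it.

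Three further inferences are tempting and not supported.

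- That a false difference would appear half the time. The 50% is the maximum of 2p(1−p), and the protocol never says that per-arm p-values will be compared.
- That Friedman is the test most markers would receive. The protocol provides for non-normal data but says nothing about how these markers are distributed.
- That the ROC analyses fail because progression may precede the 12 h or 24 h sample. The protocol gives no figure for how often that happens, and it plans diagnostic as well as predictive use, with absolute values as well as changes. That is a separate matter from the Friedman test.

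**Conclusion.** The point holds in a limited form. For non-normal repeated biomarker data the protocol names a test without a treatment term, for a question that is explicitly about treatment. This follows from the definition of the test and rests on no assumed figure. The rejection rates in the simulation are illustrations under assumed SDs and changes, and the discordance range of 9.5% to 50% for p between 0.05 and 0.95 applies only if someone compares per-arm results.

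The event-defined time adds to the problem, because it is neither a common time nor one that every patient reaches. The documents do not allow an estimate of how many patients would be lost for incomplete values.

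The reach is confined to the tertiary analysis. The primary and secondary conclusions and the sample size are unchanged.

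**What to change.** Replace the Friedman sentence, for comparisons between arms, with a method that contains the arm, applied at the fixed 12 h and 24 h times. Either of these would do:

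- a linear mixed model on log biomarker values with log baseline, sepsis stratum, treatment, time and treatment-by-time, reporting the furosemide-to-placebo ratio with its 95% confidence interval at each time; or
- a rank test on change from baseline at each time, using Mann-Whitney U or, to respect the stratified randomisation, van Elteren's test stratified by sepsis.

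Report the samples taken at RRT start, recovery or ICU discharge descriptively. Later daily samples need care if they are added to the comparison, because sampling stops when a patient leaves the study. If Friedman is kept, state that it describes change over time within an arm and that differences between arms will not be inferred from it.

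The cost is wording only: the 12 h and 24 h samples are already scheduled, and no patients or procedures are added. The change should be made before the biomarker results are unblinded.
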